partner effect _(P2–P1)_	Influence of the P2’s baseline MVPA on the P1’s post-intervention MVPA	Positive effect in intervention group, no effect in control group
Individual effects		
Actor effect _(P1)_	Stability of the P1’s MVPA from baseline to post-intervention	Intervention group < control group
Actor effect _(P2)_	Stability of the P2's MVPA from baseline to post-intervention	Intervention group < control group
Treatment effect _(P1)_	Difference between the P1’s mean post-intervention MVPA of the intervention group and of the control group	Intervention group > control group
Treatment effect _(P2)_	Difference between the P2’s mean post-intervention MVPA of the intervention group and of the control group	Intervention group > control group
Intervention effects		
Adherence	Adherence is established if BCS in the *MatchQEP* group attend at least 7 out of 10 assigned sessions with the QEP Adherence to peer support in both *MatchQEP* and *Match* groups will be established based on the number of times the peers connect (expecting at least once per week for 10 weeks)	Adherence will be established
Cost-effectiveness	Direct costs will be compared between the *MatchQEP* and *Match* groups and between the *MatchQEP* group to traditional QEP services in Canada	*MatchQEP* will be cost-effective

All research questions also align with the secondary outcomes, such that device (e.g., Fitbit) measured MVPA, social support, and HRQOL will be higher among the *MatchQEP* group.

Intervention adherence and cost-effectiveness will also be explored. We expect BCS to adhere to the *MatchQEP* group by attending at least 70% of the sessions [44, 45] and BCS to adhere to the *Match* group by connecting with their partners at least once per week for 10 weeks. We expect the *MatchQEP* group to be cost-effective (e.g., have lower direct costs compared to traditional in person and clinical QEP services in Canada and a favorable incremental cost-effectiveness ratio compared to the *Match* group). The *MatchQEP* group is also expected to report less health care use (e.g., health care facility visits, doctor visits, procedures received, support services used, and loss of work) compared to the *Match* group.

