## Methods

### Study design and participants

This is a two-arm RCT with validated outcome assessment measures. The protocol adheres to the CONSORT guidelines (Fig. 2) [46] and SPIRIT recommendations for reporting of clinical trial protocols [47]. Eligible participants are: (1) English-speaking female BCS; (2) diagnosed with primary stage 0–IV breast cancer, at any stage of treatment; (3) living in Canada; (4) aged 18 years or older; (5) medically cleared for exercise; (6) connected to the internet using any device (e.g., computer, tablet or smartphone; preferably with webcam); and (7) currently engaging in less than 150 min of MVPA per week [16–18]. Participants will be excluded from the study if they report any contraindications to exercise, or had recent or have planned surgery of any kind (including reconstructive surgery).

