#### Cost-effectiveness

The costs of the *MatchQEP* intervention will be calculated and compared to traditional face-to-face costs of QEP services in Canada and to the *Match* group alone. Refer to Table 2 for a description of costs to be compared between *MatchQEP* group and traditional QEP services. The use of health care resources will also be compared between the two groups at the post-intervention, post-tapering, and follow-up time points using a piloted questionnaire [68] that assesses health care facility visits, doctor visits, procedures received, support services used, and loss of work (see Additional file 2).

**Table 2 Tab2:** Cost of *MatchQEP* group versus traditional QEP services

*MatchQEP group*		
Program costs^#^	Professional time/labor	# of contact hours × unit cost of Qualified Exercise Professional (QEP) over the 10-week intervention period and 4-week tapering period*
	Equipment	Any device a survivor may purchase (pay out of pocket) for use at home based on the QEP’s recommendation (such as TheraBand or free weights) Computer for QEP
*Traditional QEP services*		
Session costs^#^	Total cost of QEP session	Includes venue use/cost of membership, equipment at venue, preparation time for the QEP
	Labor	# of QEP sessions attended during a comparable 10-week period × cost of each session
Travel	Mileage estimates	Based on distance (km) from an individual’s home to the session venue and the cost of gas (/km)
	Public transportation costs	
	Parking costs	
Home-based equipment		Any form of device that a survivor may purchase for use at home based on the QEP’s recommendations (for example, TheraBand or free weights)
Consumable materials	Photocopies of home exercises	
	Printed letters/folders given to survivors	

^*^For each 1-h contact cost, 1.5 h of labor will be allocated to account for the preparation time required for each session

^#^The cost of training staff will be excluded as staff will already be qualified for their role

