Multiple-group structural equation modeling (SEM) will be used to estimate and test an APIM with two groups (*MatchQEP* vs. *Match*). To address research question 1, the mean post-intervention levels of MVPA (controlling for actor and partner effects) of the two groups will be compared. For research question 2, the average partner (i.e., peer) effects of MVPA from each BCS in the dyad will be estimated within each group [43]. The effects will be tested by comparing constrained and unconstrained models on chi-square goodness-of-fit values. For research question 3, the average actor effects for MVPA among BCS will be estimated for the *MatchQEP* and *Match* groups and will be tested against each other. These analyses will be repeated for device-measured MVPA, social support, and quality of life (secondary outcomes). Measured covariates (e.g., cancer and personal characteristics, partner characteristics and quality of match, therapeutic alliance) will be included in the models as necessary based on their association with the outcomes.

To assess the intervention effects (tertiary outcomes)*,* adherence will be examined based on the number of sessions attended with the QEP in the *MatchQEP* group and on the frequency the peers connected over the duration of the study for both *MatchQEP* and *Match* participants. Cost-effectiveness will be determined by comparing the direct intervention costs between study groups and between the *MatchQEP* group and traditional, in-person QEP services. Additionally, cost-effectiveness of the intervention group, compared to control group, will be calculated based on the intervention costs per participant with respect to changes in the assessed health outcomes. Incremental cost-effectiveness ratios will determine the cost of one unit of change for the investigated outcomes. Mean costs of each category of health resource use (health care facility visits, doctor visits, procedures received, support services used) and loss of work will be calculated for each group and compared for significant differences using *t* tests. All costs will be determined based on current 2021 Ontario Health Care standards in Canadian dollars.

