Virtual delivery of exercise support also improves the ability to match BCS dyads. Not having to limit matched dyads to those who live in the same geographical area is likely to lead to more well-matched dyads (i.e., matches will include those who have similar personal and cancer-related characteristics). This is important as survivors report needing exercise programs to include those of similar age and fitness level to motivate participation [25]. Furthermore, from a behavioral change perspective, support from similar others has been found to correlate with higher levels of exercise intention and behavior in cancer survivors [84]. Finally, delivering interventions virtually is vital in order to allow exercise services to continue safely during a global pandemic [85]. Currently, few virtually-delivered exercise interventions for cancer survivors are described in the literature [76, 86–88]. While the COVID-19 pandemic has been the impetus for clinicians to quickly change the way they practice, many components of these new healthcare delivery formats will likely continue post-pandemic. Therefore, it is important to evaluate these forms of virtual interventions.

This study will also examine the cost-effectiveness of the virtual QEP intervention for BCS dyads compared to traditional in-person QEP services, as well as a partner-based intervention without QEP support. Not only will these results have immediate implications for existing dyadic exercise support programs (such as ActiveMatch [activematch.ca] and 2Unstoppable [2unstoppable.org]), but together, the findings will help to determine the most cost-effective way to deliver exercise services to cancer survivors. This information is important to convey to healthcare policy makers as QEPs, clinicians, and researchers strive to make exercise a standard component of cancer care, in a healthcare system with limited funds and space [89].

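### A lower price than traditional QEP services would be read as cost-effectiveness without effect data for them, and the ratio against Match counts programme costs only

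*Protocol article*

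**What the plan says.** The Statistical analysis section gives the rule: "Cost-effectiveness will be determined by comparing the direct intervention costs between study groups". The sentence goes on to apply the same comparison of direct costs to MatchQEP versus traditional in-person QEP services. The Cost-effectiveness section repeats the second comparison: "The costs of the *MatchQEP* intervention will be calculated and compared to traditional face-to-face costs of QEP services in Canada". Table 2 itemises both sides of it, and every entry is a cost.

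The Study purpose section offers two things as evidence that MatchQEP is cost-effective. One is that it should "have lower direct costs compared to traditional in person and clinical QEP services in Canada"; the other is a favourable incremental ratio against Match. The Discussion adds that "the findings will help to determine the most cost-effective way to deliver exercise services to cancer survivors" and names health-care policy makers as the audience.

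For MatchQEP versus Match, the Statistical analysis section adds a step in which cost-effectiveness is "calculated based on the intervention costs per participant with respect to changes in the assessed health outcomes". It then says: "Incremental cost-effectiveness ratios will determine the cost of one unit of change for the investigated outcomes". Health-care use and loss of work are collected by questionnaire in both arms at three time points, priced in Canadian dollars, averaged by category and compared by t tests. The Study purpose section expects health-care use to be lower in MatchQEP.

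**The concern.** A cost-effectiveness statement needs a difference in cost and a difference in effect between the same two options. For traditional services the plan has only the first. If MatchQEP turns out cheaper, the article's own wording would allow the trial to report it as cost-effective against in-person care. It could still be less effective than that care, and nothing in the trial would reveal it.

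Against Match both differences exist, but the ratio as written leaves out costs that the protocol itself files under cost-effectiveness. Readers could take a programme-cost figure for the full cost consequence of adding QEP support.

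**Working it through.** No cost or ratio is stated in the document, so there is no figure to reproduce. The check sets the planned comparisons against what each would need.

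**1. MatchQEP versus traditional services.** The quantity needed is ΔC/ΔE, where ΔC is cost under MatchQEP minus cost under traditional services and ΔE is the matching difference in effect.
- ΔC is available from the Table 2 items.
- ΔE is not. The design section says: "This is a two-arm RCT with validated outcome assessment measures". The arms are MatchQEP and Match. No outcome source for traditional services is named, and equal effect is not argued.
- If ΔC < 0 and ΔE ≥ 0, MatchQEP is the better option. If ΔC < 0 and ΔE < 0, it is cheaper but less effective, and a trade-off has to be judged. The planned data cannot separate these cases. The same holds, with signs reversed, if ΔC > 0.

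**2. Direct costs, MatchQEP versus Match.** Inputs: 10 weekly dyad sessions of up to 60 min (Intervention condition); 1.5 h of labour per contact hour (Table 2 footnote); no QEP contact in Match during the intervention (Control condition).
- QEP labour per dyad: at most 10 × 1 h × 1.5 = 15 h, before any tapering contact.
- Per woman: 15 / 2 = 7.5 h, against 0 h in Match.

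The direct-cost difference is therefore positive almost by design. It supplies the numerator of the ratio but cannot by itself answer the question.

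**3. The ratio against Match.** Let C be the incremental intervention cost per woman, H the difference (MatchQEP minus Match) in health-care and work-loss cost per woman, and E the difference in effect.
- Planned ratio: C/E.
- Ratio with the collected costs: (C + H)/E.
- Gap between them: H/E, whose sign follows H when E > 0.

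Illustration only; the unit cost, E and H are all assumptions. Take E = 30 min/week of MVPA and labour as the only intervention cost.

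| Assumed QEP rate (CAD/h) | C = 7.5 × rate (CAD) | C/E | (C + H)/E, H = −1000 | (C + H)/E, H = +1000 |
|---|---|---|---|---|
| 40 | 300 | 10.00 | −23.33 | 43.33 |
| 75 | 562.50 | 18.75 | −14.58 | 52.08 |
| 120 | 900 | 30.00 | −3.33 | 63.33 |

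At CAD 75/h with H = −500 or +500, the fuller ratio is (562.50 − 500)/30 = 2.08 or (562.50 + 500)/30 = 35.42. A negative entry means cheaper and more effective, a result that a numerator of programme costs alone cannot show. The table shows only that the omission can move the ratio either way. It does not estimate what will happen in this trial.

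**The case against.** The strongest reply is that the plan does not decide cost-effectiveness on price alone. Immediately after the quoted rule it relates costs to outcome changes in the randomised comparison, and the Study purpose hypothesis also requires a favourable ratio against Match. This stands. A reader might infer from the opening sentence that no cost-effectiveness conclusion is possible at all, but the text does not support that for MatchQEP versus Match.

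A second reply is that a ratio restricted to programme costs is a legitimate narrow perspective. The other costs are still reported by arm, so a reader could add the mean category costs to the programme cost. If MatchQEP does reduce health-care use as expected, the omission works against MatchQEP. All of this stands too, and a reader should not infer that the plan flatters the intervention. What remains is that the perspective is not named and the combined result is not planned.

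A third reply is that the article is open about comparing costs with traditional services: Table 2 is titled as a cost table, and the Discussion sentence is hedged. That softens the point but does not remove it, because the hypothesis and the analysis section both attach the term cost-effectiveness to that comparison.

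A reader might also suspect that the ratios would use the latent social-support and quality-of-life scores, whose unit depends on scaling. The article does not say so. It assigns the quality-of-life latent variable to the main outcome analysis, and MVPA minutes and EQ-5D-3L responses are available as denominators. That suspicion is not part of this point.

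**Conclusion.** The point holds in two parts of different weight. For traditional services the plan is wrong as written: with no arm and no effect source, the comparison supports a statement about cost and nothing further. A cost-minimisation reading would need a justification of equal effect, which the article does not give. For MatchQEP versus Match the plan is valid but narrow. Adding the health-care and work-loss costs is an improvement available from data already collected, not the correction of an error.

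How far the fuller ratio would differ, and in which direction, cannot be derived from the documents. The illustrative figures rest wholly on assumed prices, utilisation and effect. Cost-effectiveness is an exploratory tertiary outcome, and the primary analysis of self-reported MVPA is untouched.

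**What to change.** 1. In the Study purpose, Statistical analysis and Discussion sections, describe the comparison with traditional in-person QEP services as a cost comparison, and draw no cost-effectiveness conclusion from it.
2. Rest any cost-effectiveness statement on the randomised MatchQEP versus Match incremental ratio. Label the planned ratio as programme-cost perspective, and report beside it a ratio whose numerator also includes the collected health-care and work-loss costs.

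The cost is a few changes of wording and one further calculation. No new data, participants or assessments are needed.

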### Statistical analysis

All analyses will be conducted using R [73] and MPlus 7.4 [74]. Significance will be established at *p* < 0.05 for all coefficients. Descriptive statistics (means, frequencies, zero-order correlations) will be computed for all measures over time. The main analysis will be guided by APIM [41] to explore interpersonal and individual effects of the intervention (QEP support) for the primary and secondary outcomes over time.

In the APIM (see Fig. 1), effects of both dyad members are assessed simultaneously by estimating interpersonal peer effects (labelled partner effects in APIM) and individual effects (labelled actor effects in APIM). Three types of effects can be used to explore the research questions examining MVPA among BCS. First, the peer (i.e., partner) effects indicate the average influence of each BCS’s MVPA in the dyad. Second, the actor effects assess the average stability of MVPA across the intervention for each dyad member. Specifically, actor effects provide an indication to the effectiveness of the QEP support intervention since MVPA is assumed to be altered by QEP support more strongly when compared to the control group. Third, the average intervention effects will be tested and compared to post-intervention MVPA. The effectiveness of matching BCS dyads on device-measured MVPA, social support, and HRQOL will also be explored in separate models testing actor and partner effects on these secondary outcomes.

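### One expectation of lower health care use is tested as five separate category costs, possibly at three time points, and no stated analysis compares total cost between arms (minor)

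*Protocol article*

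**What the plan says.** Three sections of the protocol article bear on this.

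- **Study purpose.** After the cost-effectiveness expectation, the article adds that the MatchQEP group "is also expected to report less health care use" than the Match group. This is a single directional statement. Five components are listed in brackets as examples: facility visits, physician visits, procedures, support services and lost work. The same section labels cost-effectiveness a tertiary outcome to be explored.
- **Cost-effectiveness (Tertiary outcomes).** "The use of health care resources will also be compared between the two groups at the post-intervention, post-tapering, and follow-up time points", by questionnaire. No test is named here.
- **Statistical analysis.** The quantities to be tested are "Mean costs of each category of health resource use (health care facility visits, doctor visits, procedures received, support services used) and loss of work". This makes five items, four resource categories and one for work. On the method, the article says that they "will be calculated for each group and compared for significant differences using *t* tests". No time point is named in this sentence. The only significance level in the article is in the same section: "Significance will be established at *p* < 0.05 for all coefficients".

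The other planned cost analyses, also under Statistical analysis, use what it costs to deliver the intervention: a comparison of direct costs, and incremental ratios built on the per-participant intervention cost. Neither is a total of health-care use and lost work.

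**The concern.** One hypothesis has been given five tests, or more, with no total and no lead comparison. Two things follow.

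First, separate category tests cannot offset a saving in one category against a rise in another. If the intervention moved women from physician visits to support services at equal cost, total cost would be unchanged, yet the physician-visit test could show a significant reduction.

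Second, the chance of at least one false significant difference rises with the number of tests.

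The Discussion says the cost results should help identify the most cost-effective way to deliver exercise services and should be conveyed to policy makers. For that audience total cost matters most, and a single significant category could be taken for it.

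**Working it through.** The article states no overall error rate for these tests, so there is no figure of its own to reproduce.

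**Inputs**

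- Number of categories: 5, that is four resource categories plus loss of work (Statistical analysis).
- Number of time points: 3 (Cost-effectiveness). The t-test sentence does not say whether it applies at each time point or to costs pooled over follow-up.
- Level per test: 0.05 (Statistical analysis). It is worded for coefficients, and applying it to the t tests is a reasonable inference. Two-sided testing is assumed, so 0.025 lies in the direction favouring MatchQEP.
- Correlation among categories and across times: not given. Range assumed: 0 to 0.7.

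**Netting.** Let D1 to D5 be the true between-arm differences in mean cost. The difference in total cost is D1 + D2 + D3 + D4 + D5. If D1 = −d, D2 = +d and the rest are zero, the total difference is −d + d = 0, but the test of category 1 is a test of a real, non-zero difference. Correcting for multiple testing would not remove this, because the category finding is not a chance finding. This step needs no assumption about correlation.

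**Chance of at least one p < 0.05 with no true difference, independent tests**

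- Five tests, either direction: 1 − 0.95^5 = 0.226.
- Five tests, direction favouring MatchQEP: 1 − 0.975^5 = 0.119.
- Fifteen tests (5 × 3), either direction: 1 − 0.95^15 = 0.537.
- Fifteen tests, direction favouring MatchQEP: 1 − 0.975^15 = 0.316.

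**With positive correlation** (simulated normal test statistics, 200,000 draws, category correlation crossed with time correlation, threshold 1.96):

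| Tests | Assumed correlation | Either direction | Favouring MatchQEP |
|---|---|---|---|
| 5 | 0.3 between categories | 0.21 | 0.11 |
| 5 | 0.5 | 0.18 | 0.09 |
| 5 | 0.7 | 0.15 | 0.07 |
| 15 | 0.3 categories, 0.3 times | 0.49 | 0.26 |
| 15 | 0.5, 0.5 | 0.41 | 0.21 |
| 15 | 0.7, 0.7 | 0.30 | 0.15 |

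All these figures assume that each t test holds its 5% level. Dyads are randomised, so a t test that treats the two women of a dyad as independent would exceed that level if their costs are positively correlated. With an assumed within-dyad correlation of 0.3, the per-test error is 2 × [1 − Φ(1.96/√1.3)] = 0.086, and every figure above would be higher.

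**After the change.** A single test of total cost has a false-positive risk of 0.05, if it holds its level. Keeping all categories with a Bonferroni level would also control the risk (0.05/5 = 0.01 gives 1 − 0.99^5 = 0.049) but would leave the netting problem.

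**The case against.** The outcome is tertiary and described as explored, and control of the overall error rate is not generally required for such outcomes. Category costs are informative in themselves, since lost work and physician visits are different kinds of cost. The choice of lead time point and any adjustment are details that a condensed article may leave to a fuller document. The primary and secondary outcomes, the sample size and the incremental ratios do not depend on these tests. All of this stands, and it limits the severity.

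It does not remove the point. The article is not merely silent: it specifies testing by category, for significance, against a stated directional expectation. An analysis plan that followed it would inherit the problem.

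Two stronger readings are tempting, and the article does not support either.

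- A reader might infer that a false positive is close to a coin toss. That needs all fifteen tests to be run and to be nearly independent. The sentence that specifies t tests fixes only five, and costs from the same women are likely to be positively correlated. It also counts differences in both directions, although the expectation is one-directional.
- A reader might infer that the expectation will be declared met by whichever comparison crosses 0.05. The article states no such rule. It leaves room for that reading of the results but does not prescribe it.

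**Conclusion.** The point holds at minor severity. A single expectation is split into five category tests, possibly repeated at three time points, and no analysis stated in the article compares total health-care and work-loss cost between arms. The netting problem holds however many tests are run.

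The false-positive risk depends on the reading: about 23% for five independent tests (12% in the hypothesised direction), and at most about 54% for fifteen (32% in that direction). Positive correlation lowers these figures. They rest on a two-sided 5% level that each test actually holds and on no true difference in any category. Nothing here touches the primary result.

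**What to change.** In the Statistical analysis section, name the between-arm difference in mean total cost per woman (health-resource plus work-loss cost), from baseline to the follow-up that the article places at 26 weeks, with its 95% confidence interval, as the one test of the health-care-use expectation. Form the total by summing the three reports over recall periods that do not overlap. The questionnaire is in an additional file that is not shown, so its recall periods need to be checked first. Report the five categories and the interim time points as mean differences with confidence intervals and no significance claim.

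The change is wording only and uses data already to be collected. The small downside is that an effect confined to one category could be described but not declared significant.

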### Sample size

Sample size calculation was carried out based on APIM power analysis for indistinguishable dyads [48]. Specifically, the alpha was set to 0.05 and the sample size estimate is the smallest number of dyads required to detect the effect when power is at least 0.8. Based on standardized regression coefficient effect size estimates (beta; *ß*) drawn from a pilot study of 46 women matched for exercise (23 dyads) assessed over 21 days (i.e., reflecting the *Match* group in the current study), the actor effect size was *ß* = 0.33, the partner effect size was *ß* = 0.28, and the correlation between the two women’s self-report scores on minutes of exercise at baseline was *r* = 0.46. The correlation of the errors was set at 0.30. At minimum, 32 total dyads are needed to have adequate power to detect an actor effect and 43 total dyads are needed to have adequate power to detect a partner effect for a required sample size of *N* = 86. Attrition may be 30% [49], and 11 additional dyads will be recruited for a total sample size of 108 women (54 dyads total across both groups).

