### Treatment allocation and randomization

Dyads will be randomized (1:1) to the intervention (*MatchQEP*) or control (*Match*) group prior to baseline assessment. Treatment allocation will be centrally randomized using a web-based scheme (https://www.randomizer.org/). The randomization will be completed by a PhD student external to the research team and group allocation will be assigned in the order in which participants have completed an initial background and demographics questionnaire and have been matched with a peer for the study. Although the research coordinator(s), QEPs, and participants cannot be blinded to treatment allocation, the primary investigators and statistician completing data analysis will be blinded.

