#### Intervention condition

Participants in the *MatchQEP* group will receive exercise information and program sessions tailored by a QEP specifically for each BCS in the dyad. A single QEP, with advanced training on exercise for individuals with cancer, will provide all QEP sessions for each dyad. The study QEP also has research experience leading longitudinal and experimental trials while also holding a PhD in behavioral medicine. *MatchQEP* dyads will meet with the QEP via Zoom once per week for 10 weeks. Each weekly session will last up to 60 min and will include a review of the exercise program, achievement of goals/action plans set, adverse effects/events, and discussion on overcoming barriers to completing the prescribed exercise program. The actual length of the session, in minutes, will be noted. Additionally, the QEP will follow a standardized guide to deliver specific sessions each week based on behavior change counselling support strategies [54, 55] (see “Appendix”). Based on current exercise recommendations for cancer survivors [16–18], the overall goal of the QEP-prescribed exercise intervention is for each member of the dyad to complete a minimum of 150 min of MVPA per week, which may include both aerobic and resistance forms. Consistent with home-based exercise strategies, the QEP will tailor the program based on personal circumstances, including cancer-related characteristics, side effects, current fitness level, and available space and equipment [16]. *MatchQEP* group participants will have the opportunity to reach out to the QEP individually if they need to ask specific and personal questions during the intervention period. For 4 weeks following the completion of the 10-week intervention, the QEP will be available for consultation (i.e., a post-intervention tapering period) as needed by the *MatchQEP* group participants. This tapering period is important for understanding strategies to successfully taper BCS from exercise trials. All interactions between the QEP and the dyads from intervention initiation until the end of the tapering period will be recorded.

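### Resource-use and work-loss costs are compared by t tests with no allowance for the randomised dyad, so standard errors are too small if costs correlate positively within dyads

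*Protocol article*

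**What the plan says.** Under Treatment allocation and randomization, the unit is the pair: "Dyads will be randomized (1:1) to the intervention" or control group. Under Statistical analysis, the primary and secondary outcomes go into an actor-partner interdependence model fitted by multiple-group structural equation modelling, which represents both members of a dyad jointly.

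The cost comparison is handled differently. The same section says that mean costs for four categories of resource use and "loss of work will be calculated for each group and compared for significant differences using" t tests. It names no dyad mean, dyad random effect or cluster-robust variance, and does not say whether the observation is the woman or the dyad. The Cost-effectiveness section adds the timing: "The use of health care resources will also be compared between the two groups at the post-intervention, post-tapering, and follow-up time points".

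The Study purpose section expects the MatchQEP group to report less health care use than the Match group. These t tests are the only test the article names for that hypothesis.

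**The concern.** A two-sample t test on women assumes independent observations. Here women enter in pairs and both members always go to the same arm. The Intervention section requires partners to share a time zone, to be within 10 years of age and to be within 30 minutes per week in exercise volume. Cancer stage and treatment status enter as discrepancy scores. Partners are then in contact in both arms, and in the MatchQEP arm they also attend the weekly professional sessions together ("dyads will meet with the QEP via Zoom once per week for 10 weeks"). Some positive correlation in health care use or lost work is therefore plausible.

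If it exists, each woman carries less independent information than the test assumes, the standard error is too small and p < 0.05 is reached too often. The article accepts non-independence for exercise, support and quality of life and then leaves it out for costs. At stake is a tertiary claim that professional support lowers health care use, which the Discussion intends for policy makers.

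**Working it through.** **Inputs from the article**
- Randomised unit: the dyad, so cluster size is 2 (Treatment allocation and randomization).
- Planned size: 108 women in 54 dyads, about 27 dyads or 54 women per arm (Sample size).
- Attrition: 30%. 54 × 0.7 = 37.8, about 38 dyads or 19 per arm if dyads are lost whole.
- Level: "the alpha was set to 0.05"; two-sided is assumed.
- Correlations: "The correlation of the errors was set at 0.30", and 0.46 between partners' baseline exercise minutes in the pilot study. Both concern exercise.
- Within-dyad correlation of costs: not given. Assumed range 0 to 0.46.

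**1. The plan's own figures first.** The article states 32 dyads for the actor effect (β = 0.33) and 43 for the partner effect (β = 0.28), at 80% power. For indistinguishable dyads, with n the number of dyads:
- Residual variance = 1 − 0.33² − 0.28² − 2 × 0.33 × 0.28 × 0.46 = 0.728.
- Variance of either coefficient = (0.728/4n) × [(1 + 0.30)/(1 + 0.46) + (1 − 0.30)/(1 − 0.46)] = (0.728/4n) × 2.187 = 0.398/n.
- With the noncentral t distribution, 80% power needs 31 and 42 dyads, each one below the stated figure.

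So the within-dyad correlations have been read as the plan uses them.

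**2. Effect of ignoring the dyad in a t test.** For clusters of two the design effect is 1 + ICC. Hence:
- naive SE / true SE = 1/sqrt(1 + ICC)
- actual α = 2 × [1 − Φ(1.96/sqrt(1 + ICC))]
- effective women per arm = 54/(1 + ICC)

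| ICC | naive SE / true SE | actual α | effective women per arm |
|---|---|---|---|
| 0 | 1.000 | 5.0% | 54.0 |
| 0.05 | 0.976 | 5.6% | 51.4 |
| 0.10 | 0.953 | 6.2% | 49.1 |
| 0.20 | 0.913 | 7.4% | 45.0 |
| 0.30 | 0.877 | 8.6% | 41.5 |
| 0.46 | 0.828 | 10.5% | 37.0 |

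Example at 0.30: 1.96/sqrt(1.30) = 1.719, giving 0.0856. The SE ratio and α do not depend on the number of dyads, so attrition does not change them. A negative ICC makes the test conservative (3.9% at −0.10).

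**3. Simulation, normal data** (27 dyads per arm, 60,000 replicates). The t test on women rejects in 6.1%, 8.4% and 10.8% of trials at ICC 0.10, 0.30 and 0.46. The t test on dyad means stays between 4.8% and 5.1% from ICC 0 to 0.46.

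**4. Simulation, skewed costs** (lognormal, log-scale SD 1, same correlations on the log scale). The t test on women rejects in 5.1%, 6.9% and 8.6%; dyad means give 4.2% to 4.3%. Part of the drop arises because a log-scale correlation r is smaller on the cost scale: (e^r − 1)/(e − 1) = 0.061, 0.204 and 0.340. Step 2 at those values gives 5.7%, 7.4% and 9.0%. The remaining half point or so is the conservatism of the t test with skewed data, visible at zero correlation, where it rejects in 4.3%.

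**The case against.** The strongest reply is that the size is unknown and may be trivial. Neither 0.30 nor 0.46 is a cost correlation: one was set for the errors of the exercise model, the other is observed between women matched for exercise. Partners need not live near each other, and all costs are valued at one Ontario standard, so local prices add no correlation. At 0.05 to 0.10 the error rate is only 5.6% to 6.2%. All of this stands, and it bounds the magnitude. It does not rescue the method, because a dyad-level test is valid at every ICC, including zero.

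It can also be said that the article never states the unit of the t test. That is right: a test on women is the natural reading, not a stated fact. If dyad means are intended, one added phrase settles it.

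A reader might infer more than the article supports:
- *That the error rate is 8.6% or 10.5%.* These values rest on borrowed exercise correlations and normal data.
- *That skewed costs make the t test fail further.* The simulation does not show this; at equal latent correlation, rejection rates fell.
- *That shared sessions induce correlation throughout.* Only MatchQEP dyads have sessions with the professional.
- *That five cost categories at three time points are part of this fault.* Multiplicity is a separate matter, and a dyad-level test does not address it.
- *That intervals for the cost-effectiveness ratios are wrong.* The article plans none.

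**Conclusion.** The point holds in conditional form. The article randomises dyads, models them for the primary and secondary outcomes, and names a cost test that makes no allowance for them. If that test is run on women and costs correlate positively within dyads, the standard error is too small: by 2% to 5% at an ICC of 0.05 to 0.10, and by 12% and 17% at the upper-guide values of 0.30 and 0.46. The effect is limited because a cluster has only two members, and it vanishes at ICC 0. The mechanism is certain; the magnitude depends on a cost correlation that the article does not supply. The affected outcome is tertiary and the primary analysis is unchanged, so this is a correction worth making, not a threat to the trial's main conclusion.

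**What to change.** In Statistical analysis, replace the t tests for resource-use and work-loss costs with a t test on dyad-mean costs by arm, with about 27 dyads per arm as planned and about 19 after 30% attrition. An equivalent model with dyad as the cluster also serves, provided it carries a small-sample correction, since uncorrected cluster methods can understate uncertainty with about 20 clusters per arm. If intervals for cost differences or incremental cost-effectiveness ratios are reported, resample dyads, not women.

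The cost is one sentence in the plan and a few lines of code, with no new data and no change of design. Intervals become slightly wider if costs are positively correlated within dyads: true SE over naive SE is 1.05 at ICC 0.10 and 1.14 at 0.30.
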